## Abstract

**Background:**

Each year in the UK, ≈3000 children undergo major cardiac surgery requiring cardiopulmonary bypass. Approximately 40 % of these experience excessive bleeding necessitating red cell transfusion or treatment with other blood components. A further 40 % receive blood components because of the perception by clinicians that the risk of bleeding is high. Excessive bleeding and treatment with red cell transfusion or blood components are associated with post-operative complications such as infection and renal injury and are independently associated with increased morbidity and mortality.

Abnormalities in blood coagulation are a major cause of excessive bleeding after cardiac surgery in children. However, the extent of these abnormalities varies between children and their characteristics may change rapidly during surgery. In adults undergoing cardiac surgery, rapid testing of blood coagulation using techniques such as thromboelastometry may assist the selection of appropriate blood component treatments. In some sub-groups of adults, this improves clinical outcomes. Rapid testing of blood coagulation in children undergoing cardiac surgery has not been evaluated fully.

**Methods/Design:**

The DECISION study is a prospective, single-centre, observational study that aims to assess the utility of rapid testing of blood coagulation in children undergoing cardiac surgery. This will be achieved by testing blood samples from 200 children obtained immediately before, and after cardiac surgery. The blood samples will be analysed in parallel using thromboelastometry and reference laboratory tests of blood coagulation. The primary clinical outcome will be clinical concern about bleeding, defined as a composite of either excessive blood loss or the use of a pro-haemostatic treatment outside of standard treatment protocols because of perceived high risk of excessive bleeding. The reference laboratory test results will be used to describe the patterns of abnormalities in blood coagulation in children and will be compared to the thromboelastometry test results to determine the diagnostic accuracy of the thromboelastometry tests. We will estimate how well the reference and thromboelastometry test results predict clinical concern about bleeding.

**Discussion:**

The DECISION study will identify the most useful thromboeastometry tests of blood coagulation for the prediction of excessive bleeding in children after cardiac surgery and will inform the design of future randomised controlled trials.

**Trial registration:**

The trail was registered as ISRCTN55439761 on 23^rd^ April 2015.

## Background

Better blood and blood component transfusion is a longstanding NHS priority that is highly pertinent to cardiac surgery since the 40,000 cardiac surgery procedures in the UK each year account for 18 % of all NHS blood components used. This statistic includes 3,000 children who undergo cardiac surgery requiring cardiopulmonary bypass (CPB) and who have a 30-day mortality of 4 % and post-operative morbidity from organ injury or sepsis of about 25 % [1]. Excessive bleeding occurs in 40 % of children after cardiac surgery and is typically treated by transfusion of red cells and other blood components such as fresh frozen plasma, cryoprecipitate or platelet concentrates. However, in current NHS practice, a further 40 % of children receive blood components empirically at the end of surgery in an attempt to prevent excessive bleeding [2]. Decisions to administer blood components are not standardised and there is marked variation between NHS centres in the prevalence of excessive bleeding and in blood component use [2]. Excessive bleeding and transfusion of red cells or other components are independently associated with increased risk of post-operative morbidity and mortality arising from adverse events such as sepsis and kidney, brain and lung injury [1]. Adverse events have a significant impact on children and their families and substantially increases healthcare costs.

A major cause of excessive bleeding in children after cardiac surgery is abnormality in the blood clotting system. This is typically complex and multi-factorial and may be influenced by blood clotting abnormalities that pre-exist in the child. However, blood clotting is also affected by anaesthetic techniques that are essential for cardiac surgery to be performed. Therefore, blood clotting abnormalities vary markedly between children and change within individual children during the course of surgery [3–5]. Amongst the range of possible blood clotting abnormalities, low platelets and low fibrinogen have been most commonly observed in small single-centre or single-diagnosis groups of children and were associated with excessive bleeding [3–5]. Associations between these blood clotting abnormalities and excessive bleeding have not been tested in larger unselected cohorts.

Since different blood clotting abnormalities usually require different blood components, treatments to prevent or treat bleeding must be selected quickly and must be individualised to each patient. In adults undergoing cardiac surgery, this is currently assisted by rapid testing of blood clotting using techniques such as thromboelastometry (TEM), which is usually performed as a point-of-care test. TEM may yield diagnostically useful information about the characteristics and severity of blood clotting abnormalities during or after cardiac surgery. TEM test results are typically incorporated into simple treatment algorithms to assist selection of the most appropriate blood component or pharmaceutical treatments to reverse the blood clotting abnormality. Individualised treatment of blood clotting abnormalities informed by rapid test results has been shown to reduce red cell and blood component use in several clinical trials in adults [6–8] and to improve clinical outcomes in some patient groups [9].

Although TEM testing of blood clotting is an effective clinical strategy in adults undergoing cardiac surgery, the role of TEM testing in children is less clearly defined. In part this is because existing evidence suggests that the changes in blood clotting that develop in children during cardiac surgery are qualitatively different to those in adults and develop with different kinetics [3–5]. Consequently, diagnostic inferences from the results of TEM tests in adults cannot necessarily be extended to children and treatment decisions based on these results may not be valid. Although TEM tests are now performed after cardiac surgery in about 25 % of children in NHS hospitals [2], testing is not standardised and treatment decisions guided by TEM results have not been validated.

The *Detection of Coagulopathy in Paediatric Heart Surgery* (DECISION) Study has been developed to better define the clinical utility of blood clotting testing in children undergoing cardiac surgery and to identify areas for evaluation in future randomised controlled trials. It is anticipated that improvements in the diagnosis of blood clotting abnormalities in children will assist selection of appropriate blood components to prevent or treat excessive bleeding which may reduce blood component use and improve clinical outcomes after cardiac surgery.

## Methods and design

### Aims and objectives

The overall aim of the study is to evaluate whether TEM testing for blood clotting abnormalities in children before or after cardiac surgery will improve prediction of excessive bleeding after cardiac surgery.

This may confer direct clinical and economic benefits in two ways; 1) test results may improve selection of the best treatments for children with blood clotting abnormalities to prevent or stop excessive bleeding, and, b) test results may prevent the use of unnecessary treatments in children who do not have blood clotting abnormalities and are at low risk of excessive bleeding.

The study objectives are as follows:To describe the prevalence of the different types of blood clotting abnormality in children before and after cardiac surgery.To estimate the extent to which the TEM and reference laboratory test results predict (a) clinical concern about bleeding after cardiac surgery and (b) different types of blood clotting abnormality and clinical concern about bleeding after cardiac surgery.To estimate the diagnostic accuracy of TEM test results vs. reference laboratory tests for the different types of blood clotting abnormality identified (a) before and (b) after cardiac surgery.To investigate the agreement between the treatment recommended by the results of the reference tests and the treatment recommended by the TEM test results(see Figure 1 for study schema)

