Data collection will include the following elements: A log of all children having cardiac surgery A log of patients assessed against the eligibility criteria and, if ineligible, reasons for ineligibility. A log of potential participants or parents/guardians approached for the study (including the date when they are given the Patient Information Leaflet). Consent and baseline information, including demographic characteristics, clinical history, planned procedure. Data characterising the participant’s hospital stay Operative details Clinical observations and routinely collected laboratory test results Post-operative care Post-operative complicationsBlood clotting abnormality test results collected as part of the study will be obtained from the ROTEM device hard-drive, Multiplate device hard-drive, ETP device hard-drive, and for other tests, from the Bristol University Hospitals NHS Foundation Trust (UHBristol) electronic laboratory database. Data describing red blood cell, platelet and fresh frozen plasma transfusions will be obtained from the UHBristol blood bank electronic laboratory database. Data describing all other pro-haemostatic treatments.

A large amount of data will be available from routine sources such as medical records and intra/post-operative care charts. Study data will be recorded on a study CRF before transfer to a custom made electronic database held on a secure server. Study-specific CRFs will be used as required.

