### Statistical analyses

In order to address objective 1 (describing the prevalence of the different types of blood clotting abnormality before and after cardiac surgery) the following analyses will be undertaken:The distributions of the measurements from each reference laboratory test will be characterised separately for the two sample time-points.Principal component, latent class or similar analyses will be selected depending on the nature of the distributions and will be used to define and describe blood clotting abnormalities on the basis of the reference laboratory test results.The proportions of participants with different blood clotting abnormalities based on the classification determined in b) and with no blood clotting abnormality will be described with 95 % confidence intervals.

Logistic regression models will be fitted to estimate extent to which the individual results of the TEM and reference laboratory test results at each time point predict clinical concern about bleeding (objective 2a). Receiver operator characteristic (ROC) analyses will be performed to identify optimal cut-off criteria for predicting clinical concern about bleeding using separate analyses for each category of blood clotting abnormalities. The most prevalent clusters of abnormal reference laboratory test results (identified in objective 1) will be represented as semantic diagnostic terms representing different possible blood clotting abnormalities (e.g. increased APTT and increased anti-Xa heparin activity, but normal other reference laboratory tests indicates "residual heparin") and associations between these terms and clinical concern about bleeding will be investigated using logistic regression models (objective 2b).

We will estimate the diagnostic accuracy of TEM test results for the different types of blood clotting abnormality defined by the results of the reference laboratory tests (objective 3) by calculating the sensitivity and specificity, likelihood ratios and positive and negative predictive values for different estimates of the prevalence of blood clotting abnormality.

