The agreement between the recommended treatments resulting from the reference tests and the TEM test results will be assessed using Kappa statistics (objective 4). The proportion of participants correctly identified by diagnostic models using either TEM or reference test results will be subject to ‘optimism’ bias. Ideally, this would be addressed by validating models on ‘new’ data that is not used for developing the models (‘train-and-test’ validation). Since the sample size available for this study is not large enough to permit this, we will consider alternative methods such as cross-validation and boot-strapping.

Analyses relating to objectives 1, 2 and 3 above may additionally be stratified by age group. The primary analysis will take place when all data have been collected, samples analysed and the database is locked. No interim analysis is planned.

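### The aim is improved prediction, but the stated analyses measure only how well TEM and reference tests predict, with no clinical baseline model to improve on

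*Protocol article*

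**What the plan says.** All references are to the protocol article.

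- **Aim** (Aims and objectives). The overall aim reads: "evaluate whether TEM testing for blood clotting abnormalities in children before or after cardiac surgery will improve prediction of excessive bleeding after cardiac surgery".
- **Objective 2** (same section). The wording changes here: "To estimate the extent to which the TEM and reference laboratory test results predict (a) clinical concern about bleeding after cardiac surgery". No comparator is named.
- **Models** (Statistical analyses). Objective 2a uses logistic regression to estimate how far "the individual results of the TEM and reference laboratory test results at each time point predict clinical concern about bleeding", followed by ROC cut-offs. Objective 2b uses logistic regression on diagnostic terms built from clusters of abnormal reference tests. The section then adds: "The proportion of participants correctly identified by diagnostic models using either TEM or reference test results will be subject to" optimism bias, to be handled by methods such as cross-validation or bootstrapping.
- **Age** (Statistical analyses). Analyses for objectives 1 to 3 "may additionally be stratified by age group".
- **Data** (Study methods). The data to be collected include "Consent and baseline information, including demographic characteristics, clinical history, planned procedure", and also operative details and routine laboratory results.
- **Current practice** (Study methods). Bleeding decisions rest on clinician judgement and routine laboratory investigations.
- **Eligibility.** Weight above 2.5 kg, age up to 16 years, surgery on bypass, emergencies excluded.

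**The concern.** To say that a test improves prediction is to compare two predictions, one without the test and one with it. The analyses described give the performance of the tests themselves. They do not include a model of what is known about the child without the test, so there is nothing to subtract.

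This matters because the cohort is heterogeneous. Age, weight and planned procedure are known before either sample is analysed. If they are related both to bleeding and to a TEM parameter, that parameter will show an association and an AUC above 0.5 even when it tells the clinician nothing new. A parameter with real added value would look the same. The Discussion part of the abstract says the study will identify the most useful TEM tests and inform future randomised trials. A ranking by stand-alone performance could favour proxies for age or operative complexity.

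**Working it through.** **1. The plan's own figure.** The objective 2 power statement (Sample size calculation) takes 200 children and a 50% outcome rate. Alpha is not stated there; two-sided 0.05 is assumed, in line with the 95% intervals. With prevalence π of abnormality and relative risk RR, the risk without abnormality is p0 = 0.5 / (1 − π + π·RR), and p1 = RR·p0.

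- RR 1.5, π = 30%: p0 = 0.5/1.15 = 0.435 and p1 = 0.652, with 60 against 140 children. Power is 76.9% with the Yates-corrected chi-square (81.3% uncorrected, 80.1% by Fisher's test). The plan states 77%.
- RR 2, Yates-corrected: 78.7% at π = 4%, 85.7% at 4.5% and 90.5% at 5%. Power crosses 80% between 4% and 5%, as the plan says.

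The figures are right. They are for an unadjusted two-group comparison, so the power statement does not address improvement either.

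**2. Aim and analyses side by side.**

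| Element | What is compared |
|---|---|
| Overall aim | Prediction with TEM against an unnamed alternative |
| Objective 2a | Each test result against the outcome |
| Objective 2b | Reference-test clusters against the outcome |
| Diagnostic models | TEM results or reference results |
| Age stratification | Optional; describes subgroups and is not a comparator |

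No row contains clinical information with and without TEM.

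**3. How large could the effect be?** The documents give no gradients by age or procedure, so every input here is assumed. Take two equal age groups with bleeding risks r1 and r2 and abnormal-result rates t1 and t2, and no test effect within either group. Then:

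- π = (t1 + t2)/2
- risk if abnormal = (t1·r1 + t2·r2)/(t1 + t2)
- risk if normal = [(1 − t1)·r1 + (1 − t2)·r2]/(2 − t1 − t2)

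Middle case, risks 65%/35% and abnormal results 45%/15%:

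- π = 0.30
- risk if abnormal = 0.75 × 0.65 + 0.25 × 0.35 = 0.575
- risk if normal = 0.393 × 0.65 + 0.607 × 0.35 = 0.468
- RR = 0.575/0.468 = 1.23
- OR = (0.575/0.425)/(0.468/0.532) = 1.54

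| Risks | Abnormal results | Risk if abnormal / normal | Crude RR | Crude OR | Significant with n = 200 |
|---|---|---|---|---|---|
| 60% / 40% | 40% / 20% | 0.533 / 0.486 | 1.10 | 1.21 | 9% |
| 65% / 35% | 45% / 15% | 0.575 / 0.468 | 1.23 | 1.54 | 28% |
| 70% / 30% | 50% / 10% | 0.633 / 0.443 | 1.43 | 2.17 | 70% |

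All three keep the plan's 50% outcome rate and 30% prevalence. The last column is the power of the uncorrected two-proportion test, 60 against 140.

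**4. Continuous test.** In simulation (600 data sets per setting, n = 200), a test with no added value had correlation 0.3 to 0.7 with a clinical score whose odds ratio was 1.65 to 2.72 per SD. Alone, the test had a mean AUC of 0.54 to 0.67 and was significant in 17% to 99% of data sets. Added to the score, it was significant in about 4% to 6%, close to the nominal 5%, with an apparent AUC gain of 0.003 to 0.006. The with-and-without comparison separates the two cases; the stand-alone model does not.

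**The case against.** The strongest reply is that the numbered objectives do not promise incremental value. Objective 2 and the abstract ask how well the tests predict, and the analyses answer that. The difficulty then comes down to one word in the aim. Pure prediction also needs no adjustment for confounders: a test may predict well because it tracks age. Both points are fair. They are why rewording the aim is an acceptable remedy, but while the aim says improve, the mismatch remains.

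A second reply is that covariates may be listed in a full protocol or SAP that is not shown, and that the article never says the logistic models are unadjusted. That limits confidence in what will finally be done. It does not change what the article states: which predictors are modelled, and an aim that those models do not answer.

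Several stronger readings are tempting and are not supported:

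- *No improvement of any kind could be shown.* TEM is assessed alongside reference tests, and the two can be contrasted. The gap concerns a clinical baseline.
- *Every model uses one test alone.* Objective 2b uses clusters of reference tests, and diagnostic models on TEM or reference results are mentioned.
- *Age is ignored.* Stratification is foreseen, though only as an option and not for procedure.
- *Age or procedure will pass for test value.* No gradient is given. The mild case above yields an RR of only 1.10, and the RR of 1.43 needs steep assumed gradients.

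It is also fair that a baseline of age and procedure falls short of clinician judgement. A gain over it would be necessary evidence of improvement on current practice, not sufficient evidence.

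**Conclusion.** The point holds as a mismatch between the overall aim and the stated analyses. As written, the plan estimates stand-alone prediction and would not show that TEM improves on clinical information already available. The sample size arithmetic contains no error relevant to this point.

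The size is not measurable from the documents. Under assumed age gradients with no test effect within age, the crude RR is about 1.1 to 1.4. The upper end is near the planned 1.5, while the lower end would seldom be noticed. These figures show that the problem is possible and do not estimate bias in this study. The conclusion rests on reading improve as better than information available without the test, which the article does not define but which its description of current practice suggests. The change should be made because it is cheap and bears on which tests go forward to trials.

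**What to change.** For objective 2:

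1. Pre-specify a small baseline model from data already collected: age or weight, and planned procedure category. For sample 2, add one operative variable such as bypass duration, if it is recorded; the article lists operative details without naming it.
2. For each TEM and reference test, report the association adjusted for that baseline, the likelihood-ratio test for adding the test, and the change in AUC over the baseline. Correct the AUC change for optimism with the bootstrap or cross-validation the plan already considers.
3. For sample 2, count only outcomes in intervals B and C. Interval A ends when sample 2 is taken, so its events cannot be predicted from it.
4. Keep the single-test models as descriptive.

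**Cost.** One baseline model per sample and one augmented model for each test result already being modelled, with somewhat less precise estimates. No new participants or blood samples are needed. At the assumed 50% rate there are 200 × 0.5 = 100 events over all intervals, so the baseline must stay small. The sample 2 models may have fewer events, and the article does not give that number.

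If this is not done, reword the aim from improving prediction to predicting.

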### Study design

Prospective, single-centre, observational cohort study (see Figure 1 for study schema).

**Fig. 1 Fig1:**
[figure not shown]
Study Schema

### Study population

Children at the Bristol Royal Hospital for Children at high or moderate risk of bleeding after cardiac surgery.

### Consent

For all potential participants younger than 11 years old, the parents or guardians gave written consent after eligibility checking. For potential participants between 11 and 15 years old, signed assent was obtained from the participants and written consent from parents or guardians. The participants who were16 years old gave written consent. The study was conducted after UK Research Ethics Committee approval (NRES Committee London - City & East 13/LO/0504) in accordance with the Declaration of Helsinki.

#### Inclusion criteria

Participants may enter the study if ALL of the following apply:Cardiac surgery requiring CPB (thereby at high or moderate bleeding risk)Age ≤16 years oldWeight >2.5 Kg

#### Exclusion criteria

Participants may not enter the study if ANY of the following apply-Emergency cardiac surgeryUnable to give informed consent (16 year olds only)In foster care and parents/guardians unavailable to consent

